# Prospective evaluation of intimate partner violence in fracture clinics (PRAISE-2): protocol for a multicentre pilot prospective cohort study

**DOI:** 10.1186/s40814-018-0301-9

**Published:** 2018-06-15

**Keywords:** Intimate partner violence, Domestic violence, Orthopaedic surgery, Cohort studies, Protocol, Feasibility

## Abstract

**Background:**

One third of women experience intimate partner violence (IPV) in their lifetime. Orthopaedic health care professionals are in a good position to identify women experiencing escalating physical violence and act to promote their immediate safety, connect them to IPV resources, and reduce the risk of further harm. However, there have been no studies that explore whether experiencing a musculoskeletal injury can trigger or worsen IPV, and there have been no studies on how experiences of IPV affect orthopaedic outcomes. The primary objective of the PRAISE-2 pilot study is to assess the feasibility of conducting a large cohort study to determine the association between IPV and injury-related complications. The secondary clinical objectives are to preliminarily explore how a history of IPV affects orthopaedic outcomes and how patterns of IPV change over time following an orthopaedic injury.

**Methods:**

We will complete a pilot multicentre prospective cohort study of 250 women with musculoskeletal injuries to determine the feasibility of a multinational prospective cohort study that will determine if prior or ongoing IPV affects orthopaedic outcomes following an injury, and how patterns of IPV change over time. Our primary outcome is feasibility measured using recruitment rate (success criterion 50 patients/site in 12 months), adherence to visit windows (success criterion 75%), participant retention (success criterion 85%), and data completeness (success criterion 80%). Our secondary exploratory clinical outcomes are injury-related complications, return to function, new IPV disclosures, utilization and cost of support services, changes in abuse patterns, quality of life, and readiness to make relationship changes. We will assess feasibility based on pre-defined criteria for feasibility success and we will analyze secondary outcomes in an exploratory fashion.

**Discussion:**

The PRAISE-2 pilot study is the first step toward determining how experiences of IPV affect orthopaedic outcomes such as injury-related complications. This study will determine feasibility and assist in the development of large-scale multinational prospective IPV studies for our future IPV research program. This study will engage health care professionals from around the world to increase awareness of how IPV affects patients’ musculoskeletal and injury outcomes.

**Trial registration:**

clinicaltrials.gov NCT02529267. Registered 20 Aug 2015.

## Background

Intimate partner violence (IPV) is a pattern of physical, emotional, or sexual abuse or controlling behaviours committed by a current or past spouse or romantic/sexual partner [1]. The World Health Organization reports that one in three women globally will experience physical or sexual IPV or domestic abuse in their lives [1]. Every 6 days, a woman in Canada is killed by her intimate partner [2]. IPV is a prevalent social issue which poses significant health concerns. IPV disproportionately affects women and is a leading cause of non-fatal injury in females in North America [3, 4]. The cost of IPV in Canada is estimated at $7.5 billion annually [5]. IPV victims experience more physical and mental health problems [6, 7], including musculoskeletal injuries [8, 9], and use health care resources more frequently than non-abused women [10, 11]. A recent systematic review of 37 IPV prevalence studies reported that nearly one in four women presenting to emergency medicine and family medicine experienced IPV in their lifetime [12].

Recently, attention has started to focus on fracture clinics as an environment in which IPV is important to patient care. Health care professionals in fracture clinics have an important opportunity to identify and assist women experiencing IPV as they are well-positioned to discuss IPV with women who have presented with an injury. Compared to emergency physicians who tend to see patients once for an injury, orthopaedic surgeons often develop long-term interactions with patients over repeated follow-up clinic visits which serves to foster trust and disclosure [13]. The original PRAISE study [14], which included 2945 women globally, found that one in six women in fracture clinics experienced IPV in the year prior to completing the study. Additionally, we found that one in three injured women have experienced IPV in her lifetime [14]. Our previous research has found that IPV is more prevalent in fracture clinics within Ontario Level I Trauma Centres than in many other medical specialties [15] and the lifetime prevalence globally is similar in fracture clinics, emergency medicine, and family medicine [12, 14]. Major orthopaedic associations, such as the Canadian Orthopaedic Association [13] and American Academy of Orthopaedic Surgeons [16], have created position statements on care of patients who have experienced IPV, and they are advocating strongly for increased awareness of IPV among health care professionals who care for women with injuries.

Orthopaedic health care professionals are in a good position to identify women experiencing escalating physical violence (with resultant musculoskeletal injuries) and act to promote their immediate safety, connect them to IPV resources, and reduce the risk of further harm. It has been hypothesized that the severity of physical abuse among women presenting to fracture clinics may be higher than in other specialties [14]. Escalation of physical violence remains a key risk factor for intimate partner homicide [17]. More than one third of female homicides globally are perpetrated by an intimate partner [18] and 45% of women who are killed by their intimate partner present to a hospital for treatment of IPV-related injuries in the 2 years before their death [19]. Based on the above evidence, we argue that fracture clinics are instrumental to identifying women with more severe cases of IPV who are at greater risk of severe injury and homicide. However, more information is needed on how experiencing IPV affects musculoskeletal outcomes.

Although there is a large body of research on mental health [20] and reproductive health [21] outcomes following IPV, Sanchez-Lorente and colleagues [22] note that there is very little information on how IPV experiences affect specific physical health outcomes. Most existing studies on IPV and physical health, including the original PRAISE study, are either cross-sectional (therefore cannot assess longer-term outcomes) or report on general self-reported psychosomatic outcomes like gastrointestinal distress and headaches [22]. The fields of mental health and reproductive/maternal health have high-quality data on specific objective outcomes such as low birth weight, miscarriage, and HIV/AIDS infection [23, 24]. There is a need for studies that focus on the specifics of how IPV experiences affect physical health and objective outcomes among injured women, such as injury-related complications. If health care professionals have specific information about how IPV affects injury-related outcomes, they will be more likely to consider how IPV is affecting their patients and may be in a position to offer more individualized care. Evidence that IPV directly affects patient outcomes is necessary in order to change practice patterns of orthopaedic surgeons and other health care professionals who treat injured women. For example, health care professionals routinely inquire about smoking history when they are evaluating injured patients as there is strong evidence that smoking is associated with poor fracture healing [25]. If we have similar direct evidence that IPV affects patients’ injury outcomes, health care professionals who treat women with injuries may be more inclined to inquire about IPV routinely and potentially to adjust their treatment plan accordingly.

### Rationale for a pilot study

We chose to conduct a pilot study to assess the feasibility of enrolling and following patients in our target population and to assess the feasibility of our study procedures. Lessons learned from this pilot study will inform future prospective studies in our IPV research program. While our group was successful in recruiting patients for the original PRAISE study, that study was cross-sectional. We believe that it may be more difficult to enroll patients in a longitudinal IPV study because there is less anonymity compared to a cross-sectional study. There are also additional ethical and safety issues to consider with longitudinal IPV research compared to anonymous cross-sectional IPV studies which may affect follow-up rates. Therefore, this pilot study is needed to test the feasibility of our procedures to maximize follow-up rates while maintaining participant safety. Additionally, this pilot study will be able to inform future longitudinal IPV research on which outcomes are feasible to measure over a 1-year period in this population.

### Research objectives

#### Feasibility objectives

The primary objective of the PRAISE-2 pilot study is to determine the feasibility of a multinational prospective cohort study. Specifically, we will (1) assess our ability to recruit women across clinical sites; (2) evaluate adherence to study visit windows; (3) assess our ability to follow participants and collect data for 12 months; (4) assess our ability to collect data on our chosen clinical outcomes, including questionnaire completion; and (5) identify areas for improvement for future studies.

#### Clinical objectives

Clinical objectives in this pilot study are exploratory. The clinical objectives of the PRAISE-2 study include determining (1) how a history of IPV affects injury-related complications; (2) how a history of IPV affects return to pre-injury function; (3) incident cases of IPV after a musculoskeletal injury if the injury was not the result of IPV; (4) how a history of IPV affects health care and support service use after a musculoskeletal injury; (5) how a history of IPV affects health-related quality of life after a musculoskeletal injury; (6) how patterns of IPV change over time after a musculoskeletal injury; and (7) how abused women’s stage of change (i.e. readiness to make changes to move toward a life free from violence) changes over time after a musculoskeletal injury.

## Methods

This study was registered with clinicaltrials.gov (NCT02529267) on 20 August 2015, before the first participant was enrolled.

### Overview of the design

We plan to complete a multicentre pilot prospective cohort study of 250 women with musculoskeletal injuries to assess our ability to recruit and follow our target population, and to measure our clinical outcomes.

Important design and organizational aspects of the proposed PRAISE-2 study include (1) leveraging the international interest in IPV in surgical settings from the original PRAISE study to strengthen buy-in for this pilot cohort study; (2) broad eligibility criteria (all adult females with musculoskeletal injuries who are able to provide informed consent in a private location) ensures wide applicability of our findings beyond the centres involved; and (3) a comprehensive plan to maximize follow-up rates while maintaining patient safety.

### Patient selection

#### Eligibility criteria

We will use broad eligibility criteria to increase the generalizability of the study. The inclusion criteria are (1) adult females (at least 16 or 18 years of age depending on local ethics requirements); (2) patients presenting to participating fracture clinics within 6 weeks of their injury; and (3) patients presenting with a fracture or dislocation which is being managed with either surgical or non-surgical treatment.

The exclusion criteria are (1) unwilling to or unable to provide consent; (2) unable to complete the study questionnaires in a private location, due to safety and confidentiality; (3) unwilling or unable to follow the study protocol or their attending surgeon has concerns about their ability or willingness to follow study protocols; and (4) does not speak and write in English or the dominant language of the local clinic. Due to the sensitive nature of the topic, only patients who can consent for themselves will be considered for participation.

#### Patient screening and enrolment

All new female patients (within 6 weeks of injury) presenting to the fracture clinics of participating surgeons will be screened for participation in this study. A female research coordinator will approach each potentially eligible female patient and screen each patient for eligibility. The female research coordinator will obtain informed consent from each eligible patient who wishes to participate. Since this study will record change in IPV status over time, and we plan to make comparisons to a non-abused control group, we will follow all eligible and consenting patients regardless of whether they report experiencing IPV at baseline. We will record numbers of excluded and missed patients, and reasons for exclusion.

### Study outcomes

#### Primary (feasibility) outcomes

The primary outcome of the pilot study is feasibility including recruitment, adherence to visit windows, participant retention, and data completeness. The criteria for success of feasibility are as follows:Recruitment—Our recruitment strategy will be considered feasible if each site is able to recruit 50 participants in 12 months or less after their training call/visit.Adherence to visit windows—We have attempted to align study visit windows with clinical standard of care visits; however, standard of care visits can vary by region and/or type of injury. We expect that at least 75% of study visits should be within the defined windows in Table 1.Participant retention—While 20% loss to follow-up has traditionally been considered the industry standard [26], there is evidence from orthopaedic studies that bias begins to affect study results at even lower rates of loss to follow-up [27]. Therefore, our loss to follow-up minimization strategy will be considered feasible if loss to follow-up remains under 15%.Data completeness—Based on our experience in previous multicentre orthopaedic trauma studies, we are typically able to obtain questionnaire completeness rates of 75–85% at 12 months. Therefore, we will consider our data collection strategies to be feasible if questionnaire completion remains over 80%.

**Table 1 Tab1:** PRAISE-2 schedule of events

Assessment	Baseline (0–6 weeks from injury)	1 month (2–6 weeks from injury)	3 months (11–15 weeks from injury)	6 months (24–28 weeks from injury)	12 months (48–56 weeks from injury)
Target visit window					
Screening form	X				
Informed consent	X				
Demographic characteristics form	X				
Injury characteristics form	X				
IPV status (type, frequency, severity)	X	X	X	X	X
Assessment for complications	X	X	X	X	X
Support service utilization	X	X	X	X	X
Return to function	X	X	X	X	X
EQ-5D	X	X	X	X	X
Stages of change	X	X	X	X	X
Radiograph	(X)	(X)	(X)	(X)	(X)
Clinic notes	(X)	(X)	(X)	(X)	(X)

(X) = Only if required to adjudicate an adverse event

#### Secondary (clinical) outcomes

Since this is a pilot study, clinical outcomes will be exploratory. Clinical outcomes are (1) injury-related complications; (2) return to pre-injury function; (3) new IPV disclosures; (4) utilization and associated costs of health, legal, and social support services; and (5) changes in abuse severity/frequency and type of abuse (physical, emotional, and/or sexual IPV); (6) health-related quality of life; and (7) stage of change.Injury-related complications—Injury-related complications are adverse effects that are related to sustaining the injury or the treatment for the injury. These include bone healing problems, infection, unplanned additional surgical procedures or hospitalizations, mortality, and problems with the surgical implants requiring medical intervention. An orthopaedic surgeon who is blinded to identifying details and IPV status will adjudicate whether the event is injury-related.Return to pre-injury function—We will use the Return to Function Questionnaire (RTF) which is a four-question tool that was used in a recently completed large FDA-regulated fracture trial [28].New IPV disclosures—Women’s self-reported experience of IPV will be measured using a direct method of screening used by the PRAISE Investigators [14, 15] in two previous studies conducted in trauma populations. The tool comprises three questions with three response options (Table 2). This tool has proven feasible to administer in a trauma population and has been shown to have greater sensitivity to identify IPV compared to the partner violence screen (PVS) [29]. It is important to maximize sensitivity when screening IPV victims because not identifying victims can have many negative health and social consequences [30]. The direct method of screening can also distinguish between types of IPV (i.e. physical, sexual, and emotional abuse). A participant will be considered to have disclosed IPV if she answers positively to at least one of the three direct screening questions.Use and associated costs of health, legal, and social support services—Women’s access to and use of health and support services will be measured by directly asking participants to self-report if they have accessed health care services, a social worker, mental health professional, women’s shelter, helpline, violence against women website, or legal assistance. We will further ask participants whether they have referred a friend or family member to any of the IPV services. We will conduct a cost analysis from a societal perspective using a 1-year time horizon. Total and incremental costs will be reported as 2018 Canadian dollars for women with and without a history of IPV. Direct costs will be estimated from costs associated with injury-related complications and additionally derived from utilization of health care, social work, and mental health services. Indirect costs will be estimated from loss of productivity and time to return to function.Changes in abuse type and severity/frequency—Using the direct method of screening (Table 2), which categorizes types of violence as physical, emotional, and/or sexual abuse, we will record and analyze changes in type and severity/frequency of IPV experienced over time. Participants will be classified as experiencing no abuse, stable level of abuse, escalating abuse, and de-escalating abuse.Health-related quality of life—Participants’ quality of life will be measured using the EuroQol-5 Dimensions (EQ-5D), a widely used and well-validated quality of life tool [31]. The EQ-5D is a comprehensive, five-item compact health status classification and health state preference questionnaire.Stage of change—Participants will complete the Domestic Violence Survivor Assessment (DVSA) Short Form questionnaire to determine her stage of change. The stages of change are based on the transtheoretical model of health behaviour change applied specifically to survivors of abuse [32]. The stages of change are (1) Pre-contemplation: committed to continuing the relationship, change is not contemplated; (2) Contemplation: committed but questioning/contemplating change; (3) Preparation: considering change/exploring options to end abuse; (4) Action: victim breaks away from abusive relationship or partner stops being abusive, and (5) Maintenance: establishment of a new life apart or together. The original DVSA is well-used in IPV research and counselling and has been determined to be feasible to administer, reliable, and sensitive to change [33]. We developed the DVSA Short Form for the purpose of this study, with the aim of making the self-administered form more accessible and less time-consuming to administer in a research setting (e.g. removed gendered pronouns, removed references to having children, simplified language, removed two redundant/obsolete questions). Depending on the findings regarding feasibility of administration, we may conduct validation studies in the future.

**Table 2 Tab2:** Questions on the direct method of IPV screening questionnaire

Question	Response options		
*In the past year…*			
Have you been physically abused by your intimate partner?	Often	Sometimes	Never
Have you been emotionally abused by your intimate partner?	Often	Sometimes	Never
Have you been sexually abused by your intimate partner?	Often	Sometimes	Never
*In your lifetime…*			
Have you been physically abused by your intimate partner?	Often	Sometimes	Never
Have you been emotionally abused by your intimate partner?	Often	Sometimes	Never
Have you been sexually abused by your intimate partner?	Often	Sometimes	Never

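### The past-year and lifetime IPV items do not isolate post-injury abuse at the 1-, 3- and 6-month visits, and the disclosure rule can count earlier abuse as a new case

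*Protocol article*

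**What the plan says.** Two of the clinical objectives in the protocol article concern what happens after the injury. One is to determine "incident cases of IPV after a musculoskeletal injury if the injury was not the result of IPV"; another is how patterns of IPV change over time.

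Both are measured with the direct screening tool. Under Secondary (clinical) outcomes, the article names Table 2 as the instrument for the change outcome and states: "we will record and analyze changes in type and severity/frequency of IPV experienced over time". Each woman is then classed as having no, stable, escalating or de-escalating abuse.

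For new disclosures the rule is: "A participant will be considered to have disclosed IPV if she answers positively to at least one of the three direct screening questions".

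Table 2 prints the tool. It has three items (physical, emotional, sexual) under the stem "In the past year" and the same three under "In your lifetime". Each is answered *Often*, *Sometimes* or *Never*. No since-injury or since-last-visit version is given. Table 1 schedules IPV status at baseline and at 1, 3, 6 and 12 months. Secondary analyses reports the four classes over 12 months, and new disclosures as an incidence statistic with a 95% CI.

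**The concern.** A 12-month recall repeated at 1, 3 and 6 months looks mostly at the period before the injury, and much of it is the period already reported at baseline. A woman whose abuse stopped when she was injured must still truthfully report past-year abuse at those visits. She may drift from *Often* to *Sometimes* as abuse-free months accumulate, but she cannot reach *Never*. On the lifetime items she never can. De-escalation is thus masked at three of the four follow-ups.

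Incidence has a separate weakness. The disclosure rule speaks of three questions where Table 2 prints six across two recall windows. It does not say which window counts, or that the woman must have been negative at baseline. A woman who first mentions old abuse at month 3 meets the rule. The article itself accepts that under-reporting is possible (Identifying IPV status).

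Whether injury is followed by new or worsening IPV is a motivating question of the programme. The pilot is also meant to show which outcomes can be measured over a year (Rationale for a pilot study). Recall wording cannot be repaired once the answers are in.

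**Working it through.** The plan gives no figure of its own here, so there is none to reproduce. The check is how much of each past-year window precedes the injury.

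**Inputs.** Recall window: 52 weeks back from the visit (Table 2). Visit windows in weeks from injury (Table 1): baseline 0–6, 1 month 2–6, 3 months 11–15, 6 months 24–28, 12 months 48–56.

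**Pre-injury share** at *t* weeks after injury = max(0, 52 − *t*) / 52:

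- Baseline: 52 to 46 weeks of 52, or 100% to 88%
- 1 month: 50 to 46 weeks, or 96% to 88%
- 3 months: 41 to 37 weeks, or 79% to 71%
- 6 months: 28 to 24 weeks, or 54% to 46%
- 12 months: 4 to 0 weeks, or 8% to 0%

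**Alternative timing.** Study follow-up times the visits from baseline rather than from injury. With baseline *b* = 0 to 6 weeks after injury and visit month *m*, the share is max(0, 52 − 52*m*/12 − *b*) / 52. This gives 92–80% at 1 month, 75–63% at 3 months, 50–38% at 6 months and 0% at 12 months. The pattern is the same.

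**Overlap with the baseline recall window** = max(0, 52 − (*t* − *b*)) / 52, over the Table 1 limits with *b* = 0 to 6 and *t* no earlier than *b*:

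- 1 month: 88–100%
- 3 months: 71–90%
- 6 months: 46–65%
- 12 months: 0–19%

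The 19% is the extreme corner: baseline at week 6 and the last visit at week 48, so (52 − 42)/52 = 10/52.

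**Incidence, by case.**

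1. A truthful past-year *Never* at baseline, then a positive past-year answer. Any part of the later window that lies before baseline is contained in the baseline window, so the abuse must have occurred after baseline. This is a true incident case.
2. Earlier abuse not disclosed at baseline and disclosed at a later visit. The stated rule counts it as a disclosure, and through the lifetime items this holds however old the abuse is.
3. Abuse that began between injury and baseline, a gap of up to 6 weeks. It falls inside the baseline window and is taken as prevalent.

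The rule as written does not separate case 1 from case 2.

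**Severity.** The response options grade how often, not how severe. Change in type is visible because the three types are asked separately.

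**The case against.** A reader might infer that the incidence and change objectives cannot be answered at all. The documents do not support that. At 12 months the past-year window is 92–100% post-injury, the baseline window is 88–100% pre-injury, the wording is identical, and Secondary analyses classifies change over 12 months. That contrast is nearly clean. Incidence is also identifiable in women who truthfully answer *Never* at baseline. This stands and narrows the point. It does not remove it: the plan neither limits the change analysis to baseline against 12 months nor limits incidence to baseline-negative women. Relying on month 12 alone would also set aside three scheduled assessments.

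A reader might also want to put a size on false incidence. With 1 in 6 of 250 women positive at baseline (41.7, leaving 208.3), and an assumed 80–95% of true cases disclosed then, 41.7/0.80 − 41.7 = 10.4 down to 41.7/0.95 − 41.7 = 2.2 women would be undisclosed. That is 5.0% to 1.1% of those at risk, if all disclosed later. The disclosure rate is not in the documents, and the figure mixes abuse that had ended with abuse that continued. It is not part of the conclusion.

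Nor is it right that a woman at *Often* cannot be seen to escalate. If one type is at *Often* and another at *Never*, a newly added type shows escalation. Only *Often* on all three items is a ceiling.

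Finally, Table 1 lists severity, and the case report forms are not shown, so a follow-up stem or a severity item may exist. This limits confidence. Even so, the article names Table 2 as the measure of change and prints its items.

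**Conclusion.** The point holds in limited form. As published, the tool does not isolate post-injury IPV or de-escalation at 1, 3 and 6 months, where 88–96%, 71–79% and 46–54% of the past-year window is pre-injury. At 12 months the share is 0–8%, and the before/after comparison is nearly sound. The disclosure rule lets late disclosure of earlier abuse count as new; by how much cannot be derived from the documents.

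This rests on the Table 1 windows, on truthful answers over a full 52-week recall, and on the follow-up forms carrying the Table 2 wording. If the forms already have an interval stem, only the article's description and the incidence definition need correcting.

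The weight is moderate. The outcomes are exploratory, no p values are planned for comparative analyses, and the four feasibility criteria are untouched.

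**What to change.** - **Items.** Add the three questions with a *since your last study visit* stem at 1, 3, 6 and 12 months. Keep the past-year items at baseline and at 12 months, and base the classification of no, stable, escalating or de-escalating abuse on that matched pair. Restricting past-year items to baseline would destroy the one before/after comparison with equal windows.
- **Incidence.** Define an incident case as a woman with no past-year IPV at baseline who reports IPV since the last visit. Report first disclosure of earlier abuse separately. State that abuse concealed at baseline but ongoing would still be counted as incident.
- **Wording.** Describe movement on the *Often*/*Sometimes*/*Never* scale as change in frequency and type, unless a severity item is collected.

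The cost is three short extra items on each follow-up form, with translation and ethics notification. The interval reports cover unequal periods (about 1, 2, 3 and 6 months), so frequency answers are not directly comparable between visits. If the forms can no longer be changed, limiting the change analysis to baseline against 12 months and incidence to women negative for past-year IPV at baseline recovers most of the benefit at no data-collection cost.
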